## Methods

### Design

The study will be a multicentre, cluster-randomized controlled trial (cRCT), with hospitals as the unit of randomisation (clusters). We will include four hospitals in Bandung, Indonesia that have agreed to participate in this study. Because of the limited number of hospitals, we will use a cross-over design in which in each hospital will be given PERANTARA or control (treatment as usual (TAU)) at successive periods. Because every hospital forms its own control, the cross-over design can produce results with a smaller sample size than required with a parallel design. The order in which the hospital receives PERANTARA is randomly determined. The study will compare the PERANTARA to TAU in women with suspected breast cancer. This study uses two predefined periods. In the first period, two hospitals will have the experimental group (the patient is given the intervention and TAU) and two other hospitals will have the control group (patients only receive TAU). In the second period, it is the other way around.

The primary outcome is diagnosis delay in terms of the time between the date of the first consultation at the hospital and the date of final breast cancer diagnosis based on pathological examination. Secondary outcomes are breast cancer knowledge, anxiety and depression, and quality of life, as well as treatment delay.

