### Participants

This study will include 106 patients in the cRCT, 53 participants in the Treatment-as-Usual (TAU) control group and 53 participants in the experiment/intervention group. Power calculations suggest a minimum sample size of 41 participants per group (power = 0.80, alpha = .05 two-sided). Taking into account 30% attrition at follow-up, at least 106 participants (53 per group) need to be included. Participants will be recruited from four district hospitals in Bandung, West Java, Indonesia, that are representative for the health care facilities in the different areas in Bandung, Indonesia.

Participants will be new patients (outpatients) who visit the hospital with breast symptoms, which make them suspects of having breast cancer. Patients eligible for the intervention program will be asked to take part in the study when reporting at the district hospitals. The following inclusion criteria will be used: women with age > 18 years, an adequate command of the Indonesian language and no major psychiatric disorder. The last is determined by checking the medical record on a consultation history/record with the Psychiatric Department. Patients who have been seen by psychiatrists are excluded from the study.

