### Analysis plan

Demographic characteristics will be summarized using descriptive statistics, including percentages for categorical data, and means and standard deviations for continuous data. The descriptive statistics will be tabulated and presented graphically. Hierarchical linear modeling (HLM) will be employed to evaluate potential changes in the Diagnostic Delay Questionnaire scores over time. In this study, a three level model will be used with repeated measures nested in person, and persons nested in clusters. Time (pre, post, follow-up) will be considered as level 1, the individual persons will be considered as level 2 and the clusters (intervention-control group) will be considered as level 3. HLM analysis using a similar model will also be carried out to evaluate potential changes in the scores of secondary outcomes: Quality of Life (WHOQOL-BREF and EQ-5D 5L), HADS, and BCKT respectively. HLM analysis will be carried out separately for each phase before and after crossover. Demographic variables will be entered as additional predictors including SES, educational levels, and patients’ locations to explore potential impact on the effect of the interventions.

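### Fitting the model separately in each crossover phase, with no combined estimate stated, contradicts the own-control rationale for the design and leaves each phase a comparison of two hospitals with two others

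*Protocol article*

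**What the plan says.** The Design section of the protocol article randomises hospitals: "with hospitals as the unit of randomisation (clusters). We will include four hospitals in Bandung, Indonesia". "This study uses two predefined periods": "In the first period, two hospitals will have the experimental group" while the other two provide usual care, and "In the second period, it is the other way around". The reason given is efficiency: "Because every hospital forms its own control, the cross-over design can produce results with a smaller sample size than required with a parallel design".

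The Participants section sizes the trial as a whole: "Power calculations suggest a minimum sample size of 41 participants per group", at 80% power and two-sided alpha 0.05. This is raised for 30% attrition, so that "This study will include 106 patients in the cRCT, 53 participants in the Treatment-as-Usual (TAU) control group and 53 participants in the experiment/intervention group". These are group totals over both periods.

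The Analysis plan section describes a three-level hierarchical linear model for diagnosis delay and a similar one for the secondary outcomes. It then fixes that "HLM analysis will be carried out separately for each phase before and after crossover". It mentions no model over both periods, no period effect and no within-hospital treatment contrast.

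**The concern.** The own-control property exists only when a hospital's intervention period is compared with its usual-care period. A model confined to one phase never sees both. Each phase is then a parallel cluster trial with two hospitals per arm, the layout that the Design section says needs more patients.

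The primary outcome is most exposed. Diagnosis delay runs from first consultation to pathological diagnosis, so it depends on how each hospital works, and the baseline assessments in the Procedure section include no delay measure. Nothing within a phase removes a stable difference in speed between hospitals. The trial would also end with two estimates for one primary question, each from about half the women, and the article gives no rule for reading them together.

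**Working it through.** **Inputs from the protocol article.** Four hospitals, two periods, two hospitals per arm in each period (Design). 41 per group, 80% power, two-sided 5%, 30% attrition, 53 per group, 106 in total (Participants).

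**Assumptions not in the document.** Equal recruitment over periods and hospitals. Intracluster correlation (ICC) ρ of 0 to 0.05. Cluster autocorrelation c, the correlation of a hospital's effect between periods, of 0.5 to 1.0.

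**1. The plan's own figure.** No effect size is given, so 41 cannot be reproduced independently, only inverted. By normal approximation, d = (1.960 + 0.842) × √(2/41) = 0.619; a two-sample t-test gives d = 0.626, used below. The step to 53 reproduces as 41 × 1.30 = 53.3. (Dividing by 0.70 would give 59; that is a separate matter.) No ICC or crossover term is visible.

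**2. Size of a phase.** 106/2 = 53 women, or 26.5 per arm; after attrition 26.5 × 0.70 = 18.55 per arm. Per hospital and period, m = 106/8 = 13.25, or 9.275 after attrition. Giving both phases 41 per group needs 4 × 41 = 164 women, against 106. That count needs no assumption about recruitment.

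**3. Power at d = 0.626, two-sample t-test, ignoring clustering.**

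| Analysis | Full enrolment | After 30% attrition |
|---|---|---|
| One phase | n = 26.5 per arm: 61% | n = 18.55: 46% |
| Both periods combined | n = 53 per arm: 89% | n = 37.1: 76% |

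**4. Variance of the treatment effect (total variance 1).**

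- One phase, two hospitals per arm: V₁ = ρ + (1 − ρ)/m
- Pooled crossover, four hospitals: V₂ = [ρ(1 − c) + (1 − ρ)/m]/2

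Full enrolment:

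- ρ = 0: V₁ = 1/13.25 = 0.0755, V₂ = 0.0377, ratio 2.0.
- ρ = 0.05: V₁ = 0.05 + 0.95/13.25 = 0.1217.
  - c = 0.8: V₂ = (0.0100 + 0.0717)/2 = 0.0408, ratio 2.98.
  - c = 0.5: V₂ = (0.0250 + 0.0717)/2 = 0.0483, ratio 2.52.

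After attrition, ρ = 0.05: V₁ = 0.1524. V₂ = 0.0562 (c = 0.8) or 0.0637 (c = 0.5), so the ratios are 2.71 and 2.39.

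At ICC 0 the factor of 2.0 is simply the halved sample. Anything above it is hospital variance that the pooled contrast would largely remove.

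**5. Cluster-level test.** One phase: 4 hospitals − 2 arms = 2 degrees of freedom. Pooled: 8 hospital-periods − 1 intercept − 3 hospital − 1 period − 1 treatment = 2. Noncentral t power, with noncentrality d/√V, over ICC 0 to 0.05 and c of 0.5 to 1.0:

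| Analysis | Full enrolment | After attrition |
|---|---|---|
| One phase | 19–26% | 16–20% |
| Pooled crossover | 36–44% | 30–35% |

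**The case against.** - **The article is a condensation, and a combined estimate may be defined elsewhere.** This stands in part. The article does not say that no combination will be made, so a reader may not infer that the phases will certainly never be pooled. But separate fitting is stated affirmatively, and its natural reading covers the primary outcome. It is not a gap left for a later document.
- **The within-hospital information is not destroyed.** This is correct. Because allocation reverses, averaging the two phase estimates in a balanced trial cancels stable hospital differences. What is missing is a stated combination and a standard error that respects the hospitals shared by both phases.
- **The hospitals are randomised, so this is not bias.** This is correct. A reader might infer systematic confounding of treatment with hospital. Order is randomised, so the harm is chance imbalance, that is, added variance. The point is also weaker for knowledge, anxiety and depression, and quality of life, which have baseline values and are analysed as change.
- **The sample size did not use the crossover.** This stands. The Design section claims the saving, but 41 per group fits an ordinary two-group comparison. One cannot say that the number was derived from own-control efficiency, only that it is a total over both periods.
- **Two 5% tests inflate the error rate.** A reader might infer a familywise error of 1 − 0.95² = 9.75%. That applies only if success in either phase would be claimed and the tests are independent. The article states no such rule.
- **Four hospitals are too few under any analysis.** This is largely true. The pooled model has the same 2 cluster-level degrees of freedom, so the small-cluster penalty must be charged to both analyses.

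**Conclusion.** The point holds as a contradiction within the article. The Design section relies on each hospital being its own control, and the Analysis plan fits models in which none is. Neither that nor the shortfall against 164 women depends on an assumed effect size or ICC.

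The size of the loss does. With d back-solved to about 0.63 and equal recruitment per period, a phase estimate has 2.0 times the variance of the pooled estimate at ICC 0. At an assumed ICC of 0.05 with cluster autocorrelation 0.5 to 0.8, it has about 2.5–3.0 times (2.4–2.7 after attrition). Because the sentence governs the primary analysis, it should be changed before the data are analysed.

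A reader might infer that pooling brings the trial back to its stated 80%. The figures do not support that: pooling removes this fault, but the limit set by four hospitals remains.

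**What to change.** Replace the sentence on separate phases with wording such as: *One model will be fitted to all participants from both periods, with fixed effects for treatment, period and hospital and a random term for hospital-by-period variation. The treatment effect from this model is the single primary estimate. Phase-specific estimates are descriptive only.* The hospital-by-period term must be random, because as a fixed effect it would absorb the treatment contrast.

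Add a statement that, with four hospitals, the pooled model has only about 2 cluster-level degrees of freedom, and that power on that basis is well below 80%. If success in either phase was ever meant to support a claim, say so and control the error rate; otherwise no multiplicity adjustment arises from the phases.

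The cost is analysis-plan wording. No new data, visits or patients are needed.

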As diagnostic delay is a serious problem, efforts to reduce delay are necessary. Improving knowledge of women, via training and involving physicians and other healthcare providers, seems to be an effective approach to reduce delay in the diagnosis of breast cancer [13]. The delay to consult a doctor for seeking help after the discovery of the symptoms is most likely caused by lack of awareness and inadequate knowledge about symptoms and treatment of BC [11, 14, 15]. It is crucial that the information that is provided by the medical staff, is both informative and acceptable to patients.

A cross-sectional study in 70 breast cancer patients in Indonesia showed also that many breast cancer patients in Indonesia were not satisfied with the information they received [16]. The study showed that most patients were dissatisfied with the information about social support. Furthermore, the study found also that most of the patients were dissatisfied with the amount of written information. Therefore, the use of clear, concise, and easy to understand educational materials (e.g.: leaflets, posters, flipcharts table, visualized story telling) may be effective and efficient in complementing the verbal information that is usually provided by the oncologists at the oncology clinic. The utilization of educational material may be a solution to overcome the lack of resources (e.g. : experts, time and finance) and can be given by a face-to-face breast health education, either individually or in groups.

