Web-based programs are a promising new way to offer psycho-educational interventions to patients and their caregivers [22], but several patient groups in Indonesia have no access to it, particularly patients with low education, low socio-economic status (SES) and those in rural areas. Currently in Indonesia, printed and on-line information materials about BC have been provided by hospitals, the Ministry of Health and a number of foundations or communities. However, these sources of information appeared to not have achieved an optimal impact either, due to the lack of capacity to access them, particularly for patients with low socio-economic status (SES) in rural areas. Meanwhile, the information that is accessible to the wider public (TV, radio, and newspapers) often contains promotion of traditional healing methods which even can make patients hesitant in following the process of examination (and possible treatment) at the regular hospital.

Summarizing, several educational interventions for breast cancer patients exist, but these focus mainly on coping with cancer. Interventions which focus on the reduction in diagnosis delay, are less common, and absent in Indonesia. Therefore, an educational program to diminish diagnosis delay can be of paramount importance for reducing morbidity and death. For this purpose, we developed a psycho-educational intervention (‘PERANTARA’) focused on reducing diagnosis delay.

The aim of this study is to evaluate the effectiveness of PERANTARA in reducing the delay of breast cancer diagnosis in women who visit the hospital with BC symptoms prior to formal BC diagnosis based on pathological examination. As a secondary aim, we studied its effect on breast cancer knowledge, anxiety and depression, and quality of life. Finally, we explored the effects on the longer term, also regarding the treatment delay.

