### Procedure

The healthcare professionals (oncologist or nurse) will inform eligible participants about the study (see Fig. 1). The research assistant will follow up to inform the patients about the details of the study and asks them for oral and written informed consent. Patients who agree to participate will be asked to fill in: (1) the socio-demographic and medical history form, (2) the World Health Organization Quality of Life - Assessment Bref (WHOQOL-BREF), (3) the European Quality of Life-5 Dimensions-5 Levels (EQ-5D-5 L), (4) the Hospital Anxiety-Depression Scale (HADS) Questionnaire, (5) the Breast Cancer Knowledge Test (BCKT). Participants who are illiterate will be giving an oral consent and a thumb print in lieu of a signature, in line with recommendations from WHO [23].

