#### Secondary outcome

A standard socio-demographic and medical history form (SDMH) will be used to collect patients’ background data on ethnicity, age, marital status, religion, education level, employment status, income level, travel time to hospital, insurance status, mental health status, family history of cancer and use of traditional healer. The patients’ medical records will also be reviewed to obtain data on type and stage of cancer and type of treatment.

Patient knowledge will be assessed using the Breast Cancer Knowledge Test (BCKT). The BCKT is a 20-item questionnaire that was developed and tested to determine (a) general knowledge of breast cancer; and (b) the relationship between the knowledge of breast cancer and utilization of screening practices. The BCKT consists of 2 subscales; one subscale of 12 items to measure general knowledge and one subscale consisting of 8 items to measure knowledge of curability. In the first section, item number 3 about the breast cancer prevalence was adjusted with the actual Indonesian prevalence rate. The total score ranged from 0 to 20, with higher scores indicating higher breast cancer knowledge. The BCKT has an acceptable reliability coefficient (α = 0.69). The Breast Cancer Knowledge Test (BCKT) has been translated into Indonesian using the forward-backward translation method [24].

Symptoms of anxiety and depression will be measured with the Hospital Anxiety and Depression Scale (HADS). The HADS is a 14-item self-report questionnaire that was developed to assess psychological distress in people with medical illness. It consists of 2 subscales: 7 items to measure anxiety (HADS-A) and 7 items to measure depressive symptoms (HADS-D). Psychometric properties of the Indonesian version of the HADS were adequate, with values of Cronbach’s coefficient (alpha) being 0.77 and 0.74, respectively [13].

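### The covariate rule for the diagnosis-delay model leaves out pre-intervention breast cancer knowledge, which is already collected; adjusting for it would be a nearly free, trivial-to-moderate gain

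*Protocol article*

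**What the plan says.** The Analysis plan in the protocol article fixes both the kind of covariate and its purpose. It states: "Demographic variables will be entered as additional predictors including SES, educational levels". The sentence goes on to add patient location and says that the aim is to explore how these variables bear on the intervention effect. In that section the BCKT appears only as a secondary outcome with its own hierarchical model.

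Other sections bear on the point:

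- **Background.** Patient-related factors such as poor knowledge are called a major concern. A study in Moroccan women is cited as attributing diagnosis delay chiefly to insufficient knowledge, information and awareness.
- **Procedure.** The baseline battery includes, as its last item, "5) the Breast Cancer Knowledge Test (BCKT". It is completed before the package is handed out.
- **Procedure and Primary outcome.** Delay runs from the first hospital consultation to the pathology-based diagnosis. The delay instrument is absent from the baseline battery and appears only at the post-intervention and 3-month assessments.
- **Design.** The order of the two conditions is randomised in four hospitals. Women are then recruited individually within each hospital and period.

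**The concern.** The secondary outcomes each have a true pre-intervention score in the repeated-measures model, so that model takes account of where the women started. Diagnosis delay has no such score. Any baseline correction of the primary comparison must therefore come from other covariates, and the plan names only demographic ones, for exploration.

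The protocol's own reasoning is that better knowledge shortens delay. A baseline measure of knowledge is thus an obvious candidate for adjustment, and it is already collected. Two things are at stake: some precision in a trial of 106 women, and protection against the arms differing in knowledge when women are enrolled one by one in only four hospitals.

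**Working it through.** **Inputs from the documents.** The Participants section gives "power = 0.80, alpha = .05 two-sided" and states: "Power calculations suggest a minimum sample size of 41 participants per group". It then states: "Taking into account 30% attrition at follow-up, at least 106 participants (53 per group) need to be included". It gives no effect size or standard deviation, and no section gives a correlation between baseline knowledge and delay.

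**The plan's own figure.** Without an effect size, 41 per group cannot be reproduced, only solved backwards. By the normal approximation, d = √[2 × (1.96 + 0.84)² / 41] = 0.619 (0.626 by the t test). The step to 53 matches 41 × 1.3 = 53.3. How attrition was applied is a separate matter and is not used here.

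**Does the rule leave out the BCKT?** The list of demographic variables is open-ended, but it is a list of demographic variables. A 20-item knowledge score does not belong to that class, and the same section places it among the outcomes. As written, it is outside the delay model.

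**Is the pre-value safe to adjust for?** It is measured before the package is given, so adjusting for it does not adjust away the effect of the intervention. Later BCKT values may lie on the causal path and should not be used.

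**Gain in precision (r is assumed).** In a linear model, adjustment multiplies the residual variance by 1 − r² and the standard error by √(1 − r²). Power with n per group is Φ[d/√(1 − r²) × √(n/2) − 1.96], here with d = 0.619 and n = 41. Clustering is ignored.

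| Assumed r | √(1 − r²) | Fall in standard error | Power |
|---|---|---|---|
| 0 | 1.000 | 0% | 80.0% |
| 0.1 | 0.995 | 0.5% | 80.4% |
| 0.2 | 0.980 | 2.0% | 81.6% |
| 0.3 | 0.954 | 4.6% | 83.6% |
| 0.4 | 0.917 | 8.3% | 86.4% |
| 0.5 | 0.866 | 13.4% | 89.9% |

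**One phase at a time.** The Analysis plan analyses each phase separately, which leaves about 82/4 ≈ 20 women per arm in a phase. The same formula gives 49.9% power unadjusted, 53.6% at r = 0.3 and 61.8% at r = 0.5. Adjustment helps, but it does not make up for splitting the data.

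**Measurement error.** The r in the table refers to the observed score. If the reported reliability of 0.69 is taken at face value, a correlation of 0.3 with true knowledge becomes 0.3 × √0.69 = 0.25 with the BCKT score. Adjustment for knowledge itself is therefore only partial.

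**The case against.** The strongest objection is that the exact covariate set of a primary model usually belongs in the statistical analysis plan, which is not shown, and that the article says nothing false here. This stands so far as to make the point an improvement and not a demonstrated error. It does not remove the point, because the article is not silent. It states which class of covariate will be entered and for what purpose, and that rule leads away from the BCKT.

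A reader might also draw four stronger conclusions that the documents do not support:

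- **That use of a traditional healer is left out too.** The demographic list is open, and "family history of cancer and use of traditional healer" are items on the socio-demographic and medical history form, beside education and income. Its exclusion is not established. Nor is a woman's own healer use named as a cause of delay: the Background says that information in the public media "often contains promotion of traditional healing methods which even can make patients hesitant", which concerns promotion.
- **That every Background statement on knowledge supports the point.** The delay described as "most likely caused by lack of awareness and inadequate knowledge about symptoms and treatment of BC" is the delay before a woman consults a doctor. It precedes the primary interval. The cited Moroccan study is the relevant support.
- **That nothing else corrects the primary comparison.** The cross-over is meant to make each hospital its own control, and SES, education and location do enter the model, though for exploration. Phase-by-phase analysis weakens the within-hospital control, but that is a different problem.
- **That chance imbalance is a further bias on top of lost precision.** With 41 per group, chance alone allows a baseline difference of ±1.96 × √(2/41) = ±0.43 SD. At r = 0.3 this moves the estimate by up to 0.3 × 0.43 = 0.13 SD. That variation is already in the unadjusted standard error, so counting it again would be double counting. Imbalance arising from how women are recruited would be a real bias, but no figure in the documents allows its size to be estimated.

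Finally, the plan treats delay as a score changing over three time points although it is one interval per woman. If that model changes, the covariate can still be entered, but the √(1 − r²) gain, which is a linear-model result, may not carry over exactly.

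**Conclusion.** The point holds for the pre-intervention BCKT score only. The stated rule omits it from the diagnosis-delay model, although the protocol links knowledge to diagnosis delay, collects the score before exposure, and has no baseline value of delay to use instead.

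The gain rests on an assumed correlation and on a linear model without clustering. Below r of about 0.2 it is negligible; it becomes material from about 0.3. The documents do not show where in that range this trial falls. The second benefit, correction of measured knowledge differences between the women recruited, is real but partial given the test's reliability, and it cannot be quantified from the documents. This is a low-cost improvement, and the primary analysis is not invalid without it.

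**What to change.** Add to the Analysis plan that the main analysis of diagnosis delay adjusts for the pre-intervention BCKT total score as a prespecified fixed covariate, using the pre-value only. Report the unadjusted estimate as a sensitivity analysis. Keep the exploratory analysis of SES, education and location separate from this adjustment. Use of a traditional healer may be added as an optional second covariate.

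The adjustment goes alongside hospital and period terms and does not replace them. Naming the covariate in advance also rules out choosing covariates after the results are seen. The cost is one sentence and one degree of freedom; no new data are needed.
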